## Study design

### Participants on antimicrobial drugs

This will be a prospective observational study that will include adult patients with suspected or confirmed bacterial infection receiving amoxicillin (+/- clavulanic acid), azithromycin, ciprofloxacin. The decision to start antibiotics will be left to the managing clinician (based on clinical symptoms, full blood count, urinalysis, depending on the suspected focus) and enrolment will take place when antibiotics are initiated. We will enroll 50 participants on each of the oral antimicrobials (amoxicillin, azithromycin, ciprofloxacin). Patients being initiated on antimicrobial agents will be randomly selected, screened, and enrolled. Prescription of antibiotics will be determined by the managing clinician according to standard clinic guidelines. Participants will be requested to take the antibiotic therapy at the same time daily. At baseline, data will be collected on age, sex, gastrointestinal disorders (e.g., diarrhea and vomiting), weight, height, alcohol use, illicit drug use, and details of concomitant medications, including antiretroviral regimens. A blood sample will be drawn for measurement of serum creatinine at baseline.
Table 1 demonstrates all study procedures.

**Table 1. T1:** Study procedures.

Protocol Activity	Screen and enrolment	Day 2 +/-3days	End antibiotic Treatment	Week 2	Week 4	Week 6	Week 8
Informed Consent	x						
Clinical evaluation	x	x	x	x	x	x	X
**Laboratory**							
Serum creatinine	x						
ALT, total Bilirubin****				x **			
PK blood draw*		x		x **	x **		
Sputum cultures		x		x **	x **	x **	x **

** for participants on TB treatment where applicable

**
*Participant follow-up*
**

Study visits will be conducted at enrolment, on day 2 for measurement of drug concentrations and the last day of antibiotic use to determine treatment outcome (after 5 – 7 days).

**
*Sparse pharmacokinetic sampling for antimicrobial drugs*
**

Sampling for measurement of antibiotic concentrations will be performed on day 2 of antimicrobial therapy. Directly observed therapy will be performed on the day of the blood draw. For those on oral azithromycin and ciprofloxacin, a pre-dose sample (trough concentrations) will be drawn, while for those on amoxicillin, a pre-dose and 6-hour blood draw will be taken. (
Table 2)

**Table 2. T2:** TDM for antimicrobials.

Drug	Administration	Time of blood draw
Amoxycillin (+/- clavulanic acid)	Oral	Pre-dose, 6 hours post dose
Azithromycin	Oral	Pre-dose (trough),
Ciprofloxacin	Oral	Pre-dose (trough),

**
*Intense pharmacokinetic sampling for antimicrobial drugs*
**

Intensive pharmacokinetic sampling will be conducted after at least 2 days of oral antibiotic use, for 20 randomly selected participants on each of these oral drugs; amoxicillin, ciprofloxacin, and azithromycin. At least 20 participants were chosen based on the target of having less than 20% relative standard error in the estimated coefficient of variation. For amoxicillin, blood will be drawn pre-dose, 0.5 h, 1 h, 1.5 h, 2h, 2.5 h, 3 h, 4h, 6h, and 8 h post-dose. For azithromycin and ciprofloxacin, blood will be pre-dose, and at 1 h, 2 h, 3h, 4h, 5h, 6h, 8h, 12h, and 24h post-dose dosing.

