### Participants on anti-tuberculosis treatment

The current tuberculosis (TB) treatment involves fixed dose combinations based on weight bands, including an intensive phase of rifampicin, isoniazid, ethambutol, and pyrazinamide (RHEZ) for 2 months, followed by a continuation phase of isoniazid and rifampicin (HR) for 4 months. Dosing is determined by weight bands, with 3, 4, or 5 tablets of RHZE or HR depending on weight (<55, 55–69, ≥70 respectively). Each tablet contains 150 mg of rifampicin and 75 mg of isoniazid for both combinations. Fixed dose combinations in the intensive phase include concomitant pyrazinamide and ethambutol.

Serum rifampicin and isoniazid concentrations (C2hr, C4hr, C6hr) will be measured in participants when fasting, and following directly observed therapy, after two weeks of treatment (First TDM). Results of blood concentrations will be received within 24–48 hours and assessed to determine if the C
_max_ and AUC is within the therapeutic targets. Sub-therapeutic C
_max_ concentrations are considered less than 8mg/L and 3mg/L for rifampicin and isoniazid, respectively. AUCs for rifampicin and Isoniazid will also be considered and compared with existing published therapeutic ranges
^
22
^. Participants found to have subtherapeutic drug exposures will have dose escalation and be asked to take one additional pill of the drug that did not achieve therapeutic target concentrations (rifampicin, isoniazid or both) (
Table 3). A second blood draw for measurement of drug concentrations will be performed after another two weeks (Second TDM) and dose adjustment performed again based on the guidance in
Table 3, if concentrations are still below the target. (
Figure 1)

**Table 3. T3:** Dose adjustment table for isoniazid and rifampicin in patients with HIV.

Weight band	Normal drug levels	Sub-target INH <3mg/dl Normal RIF	Normal INH Sub-target RIF <8mg/dl	Sub-target INH <3mg/dl and Sub-target RIF <8mg/dl
<55kg	Continue INH 225 mg and RIF 450 mg (3 FDCs)	Give an additional INH tablet equivalent to: INH 300 mg	Give an additional rifampicin tablet equivalent to 600 mg dose	Give additional rifampicin and isoniazid tablets or FDCs equivalent to 300 mg INH and 600 mg rifampicin

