**Figure 1. f1:**
[figure not shown]
Therapeutic drug monitoring procedure with dose adjustment for participants on TB drugs.

If the participant is still not achieving the therapeutic target concentrations after the second C
_max_, another 1hr and 6hr blood draw will be conducted to assess for the presence of fast or delayed absorption. An additional dose adjustment with 1 additional tablet of the respective drug may be prescribed for these patients at the discretion of the study team and with consideration of observed side effects, treatment response, and concentrations attained. Those who attain therapeutic drug concentrations during TDM will revert to the previous dose. The final doses provided will be recorded for all participants.

**
*Sputum analysis*
**

For participants with tuberculosis, sputum cultures will be conducted at the Makerere University Microbacteriology laboratory. Cultures using Mycobacterium Growth Indicator tube (MGIT) and Lowenstein-Jensen (LJ) agar will be conducted within 7 days of enrolment and will be conducted every two weeks for the first eight weeks of TB treatment (intensive phase).

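### The only scheduled liver test for TB participants is at Week 2, before any rifampicin or isoniazid increase; none is scheduled after one

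*Protocol article*

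**What the plan says.** The Study design section introduces the schedule with the words "Table 1 demonstrates all study procedures". In the laboratory part of that table, the row "ALT, total Bilirubin" has one mark, under Week 2, and the mark's footnote limits it to TB participants where applicable. Clinical evaluation is marked at every visit, including Weeks 4, 6 and 8.

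Under Participants on anti-tuberculosis treatment, rifampicin and isoniazid levels are first measured after two weeks of treatment. "Results of blood concentrations will be received within 24–48 hours", and participants below target then take an additional tablet of the drug concerned. A second draw "will be performed after another two weeks (Second TDM) and dose adjustment performed again based on the guidance in" Table 3. For those still below target, the text after Figure 1 says that "another 1hr and 6hr blood draw will be conducted to assess for the presence of fast or delayed absorption". A further tablet may then be given "at the discretion of the study team and with consideration of observed side effects, treatment response, and concentrations attained". It also says: "Those who attain therapeutic drug concentrations during TDM will revert to the previous dose".

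Safety assessment leaves the remaining safety tests to standard of care and requires adverse event reporting for participants whose TB doses are adjusted. Data Monitoring Committee sets up a board that periodically reviews toxicity in the same group.

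**The concern.** The protocol chose ALT and bilirubin as a study test for TB participants and fixed when it is done. At that time it can give a pre-escalation reference but cannot show any effect of the escalation. The higher dose is a study intervention, triggered by study drug levels, so routine care is not timed to it.

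Two decisions suffer. The study team must weigh side effects before adding a further tablet after the Week 4 levels, and the monitoring board must judge toxicity in escalated participants. Neither would have a planned liver value on the higher dose to set against the Week 2 value. Adverse drug reactions are also a listed outcome for the TB group. Reporting that depends on what staff see or participants mention will not pick up an enzyme rise without symptoms unless someone measures it.

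**Working it through.** The plan states no figure for this point, so the check is to read the table by cell position, set it against the dosing timeline, and then size the gap.

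**1. Column alignment in Table 1**

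| Row | Enrolment | Day 2 | End of antibiotic | Wk 2 | Wk 4 | Wk 6 | Wk 8 |
|---|---|---|---|---|---|---|---|
| Clinical evaluation | x | x | x | x | x | x | x |
| ALT, bilirubin | | | | x | | | |
| PK draw | | x | | x | x | | |
| Sputum culture | | x | | x | x | x | x |

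By the same cell count, the PK row matches the first and second drug-level draws at Weeks 2 and 4. The sputum row matches the two-weekly cultures over eight weeks described under Sputum analysis. The columns have therefore not shifted, and the liver mark belongs to Week 2.

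**2. Timeline for a TB participant**

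| Time | Dosing event | Liver test scheduled |
|---|---|---|
| Week 2 | First levels drawn, dose unchanged | Yes |
| Week 2 + 24–48 h | First possible increase | No |
| Week 4 | Second levels, further adjustment possible | No |
| After Week 4 | 1 h and 6 h draw, possible further tablet | No |
| Weeks 6 and 8 | Clinical evaluation and sputum | No |

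Scheduled visits after the first increase: Weeks 4, 6 and 8. Of these, 0 of 3 include ALT or bilirubin. Calendar time after the only test: 8 − 2 = 6 weeks, and 6/8 = 75% of the intensive phase.

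**3. Size of the first step (Table 3)**

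- Below 55 kg: isoniazid 225 to 300 mg, rifampicin 450 to 600 mg; 75/225 = 150/450 = 33.3%.
- 55–69 kg: 300 to 375 mg, 600 to 750 mg; 75/300 = 150/600 = 25%.
- 70 kg and above: 375 to 450 mg, 750 to 900 mg; 75/375 = 150/750 = 20%.

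The doses reached by any later step are not printed.

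**4. Time on the higher dose at Week 4**

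The dose rises at day 14 plus 24–48 h, which is day 15–16. At day 28 that gives 28 − 16 = 12 to 28 − 15 = 13 days, or 14 days if the second fortnight is counted from the increase. Reversion for those at target follows from the Week 4 result, so everyone escalated is still on the higher dose at that draw.

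**5. How many participants**

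Inputs: 25 TB participants and 15% withdrawal (Sample size); 78% below target for rifampicin and 84% for isoniazid in the SOUTH dataset (Statistical analysis). It is an assumption that these rates apply here. The overlap between the two drugs is not given, so the share with at least one drug low lies between

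- max(0.78, 0.84) = 0.84, and
- min(1, 0.78 + 0.84) = 1.00.

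Of 25: 25 × 0.84 = 21, up to 25. After withdrawal: 25 × 0.85 = 21.25, then 21.25 × 0.84 = 17.9, so about 18 to 21.

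**The case against.** The strongest reply is that the evidence is incomplete. The liver row carries its own four-asterisk marker, whose explanation is not in the text, and Figure 1, which shows the dose-adjustment procedure, is not visible. Either could call for repeat tests. This is also a condensed article, and Table 1 is not exhaustive: it has no entry for the later 1 h and 6 h draw. These points stand as caveats. They do not make this a mere omission, because the article itself prints a liver test and places it where it can only precede the increase.

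A second reply is that safety after escalation is covered by clinical evaluations at Weeks 4, 6 and 8, graded adverse event reporting in dose-adjusted participants, standard care and a monitoring board. These safeguards are real, and nobody should read this point as saying that liver monitoring is impossible. But none of them, as printed, sets a liver value after escalation.

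A third reply concerns size, and part of it stands. The 75% is calendar time, not time on a higher dose; participants who reach target go back to the previous dose and may have had only about two weeks of escalation. Because AUC is also considered, the escalated share in this study is unknown. In the two lower weight bands, the first-step dose equals the routine dose of the next band up. The documents contain no estimate of added liver risk. All this limits what can be said about harm, but it does not change the order of test and dose increase.

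**Conclusion.** The point holds on the printed text. The only scheduled ALT and bilirubin test comes 24–48 hours or more before the first possible dose increase, and none of the three later visits repeats it. The increases are 20–33% at the first step, with at least one further step possible. Under the assumption that the SOUTH rates carry over, 84–100% of the TB group would be affected: 21–25 of 25, or about 18–21 after withdrawal.

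The conclusion concerns scheduled tests only and makes no claim that harm will occur. Confidence is medium because the row's footnote, Figure 1 and the full protocol could not be seen. It is a change that should be made, as it is cheap and bears on participant safety and on the dose decision after Week 4.

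**What to change.** Keep the Week 2 test as the pre-escalation reference. For participants whose dose was raised, add ALT and total bilirubin to the Week 4 draw and require the result before any further dose step. For those escalated again at or after Week 4, repeat both tests at the 1 h and 6 h draw if the new dose has started by then, otherwise at the Week 6 or Week 8 visit. If the four-asterisk footnote or the full protocol already requires this, show it in Table 1 and print the footnote.

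Cost: an amendment to Table 1 and two assays per escalated participant on an existing sample, so 2 × 21 = 42 to 2 × 25 = 50 assays at Week 4 under the SOUTH assumption. Repeats after a second escalation add between 0 and 50 assays, since that share is not given, and may need one small extra sample. The liver result must return within the 24–48 hours already allowed for drug levels, or it will delay the second dose decision. Assay prices are not in the document.

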### Patients on intravenous antibiotics (Ceftriaxone)

Patients who are acutely ill and admitted in the in-patient wards of Mulago hospital will be enrolled for pharmacokinetic sampling while on ceftriaxone. Blood draws will occur when a patient has received at least 1 dose. A blood draw will be taken prior to dosing (Ctrough) and again, 2 hours after completion of bolus administration for ceftriaxone. Participants will be followed up to determine treatment outcome at the end of treatment or at discharge.

### Participants on anti-tuberculosis treatment

The current tuberculosis (TB) treatment involves fixed dose combinations based on weight bands, including an intensive phase of rifampicin, isoniazid, ethambutol, and pyrazinamide (RHEZ) for 2 months, followed by a continuation phase of isoniazid and rifampicin (HR) for 4 months. Dosing is determined by weight bands, with 3, 4, or 5 tablets of RHZE or HR depending on weight (<55, 55–69, ≥70 respectively). Each tablet contains 150 mg of rifampicin and 75 mg of isoniazid for both combinations. Fixed dose combinations in the intensive phase include concomitant pyrazinamide and ethambutol.

Serum rifampicin and isoniazid concentrations (C2hr, C4hr, C6hr) will be measured in participants when fasting, and following directly observed therapy, after two weeks of treatment (First TDM). Results of blood concentrations will be received within 24–48 hours and assessed to determine if the C
_max_ and AUC is within the therapeutic targets. Sub-therapeutic C
_max_ concentrations are considered less than 8mg/L and 3mg/L for rifampicin and isoniazid, respectively. AUCs for rifampicin and Isoniazid will also be considered and compared with existing published therapeutic ranges
^
22
^. Participants found to have subtherapeutic drug exposures will have dose escalation and be asked to take one additional pill of the drug that did not achieve therapeutic target concentrations (rifampicin, isoniazid or both) (
Table 3). A second blood draw for measurement of drug concentrations will be performed after another two weeks (Second TDM) and dose adjustment performed again based on the guidance in
Table 3, if concentrations are still below the target. (
Figure 1)

**Table 3. T3:** Dose adjustment table for isoniazid and rifampicin in patients with HIV.

Weight band	Normal drug levels	Sub-target INH <3mg/dl Normal RIF	Normal INH Sub-target RIF <8mg/dl	Sub-target INH <3mg/dl and Sub-target RIF <8mg/dl
<55kg	Continue INH 225 mg and RIF 450 mg (3 FDCs)	Give an additional INH tablet equivalent to: INH 300 mg	Give an additional rifampicin tablet equivalent to 600 mg dose	Give additional rifampicin and isoniazid tablets or FDCs equivalent to 300 mg INH and 600 mg rifampicin
55–69kg	Continue INH 300 mg and RIF 600 mg (4 FDCs)	Give an additional INH tablet equivalent to INH 375 mg dose	Give an equivalent rifampicin tablet equivalent to 750 mg dose	Give additional rifampicin and isoniazid tablets or FDCs equivalent to 375 mg INH and 750 mg rifampicin
≥70kg	Continue INH 375 mg and RIF 750 mg (5 FDCs)	Give an additional INH tablet equivalent to 450 mg dose	Give an additional rifampicin tablet equivalent to 900 mg dose	Give additional rifampicin and isoniazid tablets or FDCs equivalent to 450 mg INH and 900 mg rifampicin

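### At the second drug-monitoring round, Table 3 returns the dose already being taken for a drug that was escalated at the first, while the text calls for a further step

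*Protocol article*

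**What the plan says.** The section on participants on anti-tuberculosis treatment gives the tablet content ("Each tablet contains 150 mg of rifampicin and 75 mg of isoniazid for both combinations") and the starting dose ("with 3, 4, or 5 tablets of RHZE or HR depending on weight (<55, 55–69, ≥70 respectively"). Therapeutic drug monitoring (TDM) takes place after two weeks of treatment, and participants below target are to "be asked to take one additional pill of the drug that did not achieve therapeutic target concentrations". Two weeks later comes the second round: "A second blood draw for measurement of drug concentrations will be performed after another two weeks (Second TDM) and dose adjustment performed again". The guidance named for this second adjustment is again Table 3.

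Table 3 has one row per weight band and four columns: both drugs normal, isoniazid low, rifampicin low, both low. It has no row or column for the monitoring round or for the current dose. Two of its cells read "Give an additional INH tablet equivalent to: INH 300 mg" (below 55 kg, isoniazid low) and "Continue INH 300 mg and RIF 600 mg (4 FDCs" (55–69 kg, both normal).

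The paragraph after Figure 1 deals with participants still below target after the second peak concentration. It provides for further blood draws to look at absorption and adds: "An additional dose adjustment with 1 additional tablet of the respective drug may be prescribed". That step is at the study team's discretion. The same paragraph says that those who reach target go back to the previous dose, and that final doses will be recorded.

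**The concern.** The table that governs the second adjustment was built for the first. It starts from the unescalated dose and names one dose per cell. For a drug already raised at the first round and still low at the second, the table and the sentence that points to it give different instructions.

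The second study objective is the utility of TDM in reaching targets for rifampicin and isoniazid, and the statistical analysis section evaluates whether dose adjustment achieves those targets. If the strategy has a different number of steps depending on which instruction staff follow, then the doses reached after the second round, and the adverse reactions on them, do not describe one defined intervention. The Data Monitoring Board is asked to review toxicity in these same participants, and the article does not say at what dose escalation ends.

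**Working it through.** **Inputs**, all from the section on participants on anti-tuberculosis treatment and Table 3: each tablet holds 150 mg rifampicin and 75 mg isoniazid; starting tablets n = 3, 4, 5 for <55, 55–69 and ≥70 kg.

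**Step 1. Reproduce Table 3.** Normal-level cell = n × 75 mg isoniazid and n × 150 mg rifampicin. Sub-target cell = (n + 1) × 75 and (n + 1) × 150.

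| Band | n tablets (INH/RIF, mg) | Table 3, normal | n + 1 tablets (INH/RIF, mg) | Table 3, sub-target |
|---|---|---|---|---|
| <55 kg | 225/450 | 225/450 | 300/600 | 300/600 |
| 55–69 kg | 300/600 | 300/600 | 375/750 | 375/750 |
| ≥70 kg | 375/750 | 375/750 | 450/900 | 450/900 |

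Every cell is reproduced exactly, so the sub-target figures are totals one tablet above the start.

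**Step 2. Test the other reading**, that the figures are amounts to add. For <55 kg this gives 225 + 300 = 525 mg isoniazid and 450 + 600 = 1050 mg rifampicin after one adjustment, an addition of 600/150 = 4 tablet-equivalents. For the other bands the additions are 750/150 = 5 and 900/150 = 6. This contradicts the one-pill rule, so the total-dose reading is the one that fits.

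**Step 3. Apply Table 3 at the second round** to a participant escalated on a drug at the first round and still low on that drug. Change = sub-target cell − dose already held:

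- <55 kg: 300 − 300 = 0 mg isoniazid; 600 − 600 = 0 mg rifampicin
- 55–69 kg: 375 − 375 = 0; 750 − 750 = 0
- ≥70 kg: 450 − 450 = 0; 900 − 900 = 0

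**Step 4. Follow the text instead**, with one tablet-equivalent per adjustment. Total after k adjustments = (n + k) × 150 mg rifampicin and (n + k) × 75 mg isoniazid; relative rise = k/n for both drugs.

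| Band | k = 1 (INH/RIF, mg) | k = 2 | k = 3 |
|---|---|---|---|
| <55 kg | 300/600 (+33%) | 375/750 (+67%) | 450/900 (+100%) |
| 55–69 kg | 375/750 (+25%) | 450/900 (+50%) | 525/1050 (+75%) |
| ≥70 kg | 450/900 (+20%) | 525/1050 (+40%) | 600/1200 (+60%) |

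Only the k = 1 total stands in each band's own row of Table 3.

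**Step 5. Count the steps.** Following the table gives one step. Following the text gives two if the tablet described after Figure 1 is the second-round adjustment itself, and three if it comes on top of that adjustment. Both provisions are triggered by a concentration still below target at the second round, so the article does not settle which is meant.

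**Step 6. Place this on the schedule.** Table 1 schedules the tuberculosis pharmacokinetic draws at weeks 2 and 4. The week 4 draw is the second round. It therefore measures the effect of the first adjustment, on which table and text agree, before any second adjustment is made.

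**The case against.** Several points on the other side have force.

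- **Three steps are not established.** A reader might infer that the text plainly allows three. Because the two provisions share a trigger, two is as fair a reading. This stands, and the size is therefore given as a range. On either reading the table stops after one step.
- **The gap is confined to a drug already escalated.** A drug first found low at the second round gets a genuine step from Table 3. This stands.
- **The table is not unreadable when one drug has reached target.** A reader might infer that someone escalated on both drugs and now low on only one has no entry. The single-drug columns are indeed silent on the dose of the other drug, but the sentence about going back to the previous dose supplies a rule for a drug that has reached target. The stronger inference is not supported.
- **Attainment at the second round is not mixed.** A reader might infer that the main target-attainment result is compromised. Step 6 shows that it is not. What can differ is later dose, adverse reactions and any later concentration, such as the draws described after Figure 1.
- **The cells' wording about giving an additional tablet can be repeated.** It can, but the total written in the same cell is then exceeded, so the conflict remains.
- **Figure 1 may set out the sequence.** It was not available for this review and could settle the number of steps. A dose limit may also sit in the full protocol. Neither would change the cells of Table 3, which the text names as the guidance for the second round.
- **Safeguards exist.** The tablet described after Figure 1 is discretionary and weighed against side effects, final doses are recorded, adverse events are collected in dose-adjusted participants, and a board reviews them. These limit the harm and help description afterwards, but they do not define the strategy beforehand.

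**Conclusion.** The point holds as a conflict between a stated dosing instruction and the table it relies on. For a participant already escalated on a drug and still low on it, Table 3 gives a change of 0 mg in all three bands, while the text calls for adjustment again: "dose adjustment performed again based on the guidance in" Table 3. By ascending weight band, the highest rifampicin total is 600/750/900 mg with one step, 750/900/1050 mg with two and 900/1050/1200 mg with three; isoniazid rises in the same proportion.

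This rests on two assumptions: that the Table 3 figures are totals, which the arithmetic supports, and that each further adjustment is one fixed-dose tablet-equivalent, as in Table 3. The article gives no strength for single-drug tablets.

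The number of participants affected cannot be stated. The article gives no share expected to remain below target at the second round; the proportions it cites from the SOUTH dataset were measured without dose adjustment.

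The consequence is limited to what follows the second round: the dose reached, adverse reactions and any later concentrations. It still merits correction, because it concerns the content of the intervention and participant safety.

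**What to change.** Reconcile Table 3 with the second-round sentence and with the paragraph after Figure 1:

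- Give the table an entry for a participant already escalated on one or both drugs, for example by indexing it on current dose as well as weight band, and keep it consistent with the sentence on going back to the previous dose.
- State whether the tablet described after Figure 1 is the second-round adjustment or a further one, and where escalation ends. Both are for the clinical team to decide; no dose or rule is proposed here.
- Check that Figure 1 shows the same sequence.
- Report adverse reactions and any concentrations measured after the second round by dose reached. The final doses are already to be recorded.

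The cost is a revision of one table and the matching wording. These changes in themselves add no participants, visits or samples.

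### A below-target second TDM meets two unreconciled dosing rules, so 0, 1 or 2 further tablets can follow from the same result

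*Protocol article*

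**What the plan says.** All of this stands in the protocol article, section Participants on anti-tuberculosis treatment, including Table 3 and the text after Figure 1.

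- **First TDM (after two weeks).** A participant below target is to "be asked to take one additional pill of the drug that did not achieve therapeutic target concentrations". This step is fixed.
- **Second TDM (two weeks later), text before Table 3.** "Second TDM) and dose adjustment performed again based on the guidance in" Table 3, "if concentrations are still below the target". No discretion is mentioned.
- **Second TDM, text after Figure 1.** The condition opens "If the participant is still not achieving the therapeutic target concentrations after the second C" (the sentence continues to Cmax). The action is that "another 1hr and 6hr blood draw will be conducted to assess for the presence of fast or delayed absorption". One more tablet of the drug concerned then "may be prescribed for these patients at the discretion of the study team and with consideration of observed side effects", treatment response and the concentrations attained.
- **Tablet strength.** "Each tablet contains 150 mg of rifampicin and 75 mg of isoniazid for both combinations".
- **Schedule.** Table 1 marks PK draws for TB participants at weeks 2 and 4, and none at weeks 6 or 8.
- **Analysis.** The Statistical analysis section will evaluate whether dose adjustment leads to target attainment, which is Objective 2.

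**The concern.** Both instructions appear to act on the same event, a second TDM below target. One orders an adjustment. The other orders a diagnostic draw and makes the adjustment optional. Nothing in the text says how they combine.

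Three things are at stake:

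- **Dosing.** Two team members following the text in good faith could give different numbers of tablets for the same result, and the total number of escalation steps is not fixed.
- **Safety review.** The Data Monitoring Committee section counts events among participants receiving dose adjustment. An unfixed number of steps makes that group harder to interpret.
- **Later results.** If the further tablet depends on side effects and response, then dose after week 4 is tied to the outcomes it would be related to. Any attainment, exposure-response or toxicity summary using those later doses carries that confounding.

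**Working it through.** **1. The two rules side by side**

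| | Text before Table 3 | Text after Figure 1 |
|---|---|---|
| Trigger | Still below target at the second TDM | Still below target after the second Cmax |
| First action | Dose adjustment per Table 3 | 1 h and 6 h draw |
| Further tablet | Stated without discretion | Optional, at discretion |
| Later measurement that would separate the rules | None in Table 1 | None in Table 1 |

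**2. What Table 3 encodes**

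Reading each cell as a total daily dose, adjusted dose = (standard tablets + 1) × 150 mg rifampicin or 75 mg isoniazid:

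- <55 kg: (3+1) × 150 = 600; (3+1) × 75 = 300
- 55–69 kg: (4+1) × 150 = 750; (4+1) × 75 = 375
- ≥70 kg: (5+1) × 150 = 900; (5+1) × 75 = 450

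All six match Table 3. The table is indexed by weight band, not by current dose, and holds one step. Applied again literally, it returns the dose the participant already takes.

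**3. Doses open after a failed second TDM**

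Take <55 kg, below target on both drugs, started at 450/225 mg and already escalated once to 600/300 mg (rifampicin/isoniazid):

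- Table 3 cell applied again literally: 600/300 (0 further tablets)
- Adjustment read as one further tablet: 750/375 (1)
- Discretionary rule alone: 600/300 or 750/375 (0 or 1)
- One further tablet, then the discretionary tablet: 750/375 or 900/450 (1 or 2)

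Against 450 mg, rifampicin is up by 150/450 = 33%, 300/450 = 67% or 450/450 = 100%. In the other bands the same readings give 750, 900 or 1050 mg (55–69 kg) and 900, 1050 or 1200 mg (≥70 kg). The spread is 300 mg rifampicin and 150 mg isoniazid in every band.

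**4. How many participants might reach this branch**

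The documents do not give this, so it rests on assumptions. Taken from the documents: 78% below the rifampicin target without dose adjustment (SOUTH dataset, Statistical analysis), 25% CV in exposure and 25 participants (Sample size). The one-tablet step multiplies the dose by f = 4/3, 5/4 or 6/5, that is, by 1.33 down to 1.20. Assumed: the SOUTH share carries over, the 25% CV applies to Cmax, Cmax is lognormal and proportional to dose, and there is no within-person variability.

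Share of all TB participants still below target = Φ(z − ln f / σ), with z = Φ⁻¹(0.78) = 0.772 and σ = √ln(1 + CV²).

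At CV 25%, σ = √ln(1.0625) = 0.246:

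- f = 1.33: Φ(0.772 − 0.288/0.246) = Φ(−0.396) = 0.346; × 25 = 8.7
- f = 1.20: Φ(0.772 − 0.182/0.246) = Φ(0.032) = 0.513; × 25 = 12.8

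So about 9 to 13 of 25. As a sensitivity check with CVs that the documents do not state:

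- CV 40%: 0.510 to 0.618, about 13 to 15 of 25
- CV 60%: 0.600 to 0.671, about 15 to 17 of 25

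Without the model, 78% to 84% of 25 is 19.5 to 21 below target at the first TDM. If anywhere from 10% to 75% of these stay below, the count is 0.10 × 19.5 ≈ 2 to 0.75 × 21 ≈ 16.

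**The case against.** **A sequence may be intended.** The second instruction speaks of an additional adjustment, which fits a Table 3 step first, then the absorption draw, then an optional extra tablet. This is a fair reading. The text does not state it, however. The later rule is tied to the second Cmax and not to a measurement taken after re-adjustment, and no third TDM is scheduled. If the sequence is intended, two further tablets could follow from one result, and the text should say so.

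**Figure 1 may settle the order.** It is cited directly after the disputed sentence and is not shown here. This limits the point to the visible text. Even so, the two written instructions would have to agree with the figure.

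**Objective 2 is largely protected.** This stands. The first escalation is one fixed step, and week 4 is the last scheduled attainment measurement. A reader might infer that the whole TDM strategy is undefined, or that the Objective 2 result is confounded throughout. The documents do not support that: the ambiguity begins only once the second TDM result is known. The exploratory culture comparison of adjusted with non-adjusted participants is also hardly touched, because anyone who reaches this branch after a first escalation already counts as adjusted.

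**Discretion is not a defect in itself.** This also stands. A single stated discretionary rule would be acceptable, and final doses are recorded for all participants. That record shows what was given, but not which rule was followed or why.

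**Conclusion.** The point holds for the step after the second TDM. The visible text gives two instructions for one result without saying how they relate, and it admits 0, 1 or 2 further tablets, a spread of 300 mg rifampicin and 150 mg isoniazid. The consequence is for dosing, safety reporting and any exposure or attainment result after week 4.

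Two stronger inferences should not be drawn. The first is that either rule alone leads to two tablets above the starting dose, or that the text before Table 3 gives every such participant a second increase. Table 3 applied again literally gives no increase, so that is only one reading. The second is a firm count of those affected. About 9 to 13 of 25 depends on the carried-over 78%, the 25% CV, lognormal Cmax, dose proportionality and no within-person variability. Larger variability between participants raises the count, and a more than proportional rise of Cmax with dose would lower it. The inconsistency itself does not depend on the count.

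It merits correction before more participants reach this step. It does not undermine the attainment result at the second TDM.

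**What to change.** 1. Reconcile the text before Table 3, the text after Figure 1, Table 3 and Figure 1 into one rule for a below-target second TDM. The rule should state whether the adjustment is automatic or discretionary, whether it comes before or after the 1 h and 6 h draw, and the maximum number of steps. Which clinical rule applies is for the investigators to decide.
2. State that Objective 2 attainment is the second TDM value, reached under the fixed first step.
3. Report any later step separately and descriptively, with the reason for giving or withholding the tablet recorded.

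The cost is protocol wording, one additional case record form field and a stated reporting split. No extra participants or visits are needed.
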